### Study design

This study is a single cross-sectional survey targeting 18,500 AGYW, to be conducted in 2017/2018 in four selected districts in South Africa. AGYW between 12 and 24 years will be selected using a stratified cluster-based sampling approach, with districts representing strata and the cluster or primary sampling unit being the small area layers (SALs). SALs were created by merging adjacent Enumeration Areas (EA), which had less than 500 people, to create a spatial area layer that corresponded as closely as possible to the EA layer. The following criteria were used for the establishment of the SALs. EAs were merged if they fell within the same sub-place (a higher order geographic level); EAs were merged if they had the same geographical properties; an EA was merged if its population that resided there was less than 500 people; and lastly, the resulting SALs must have a population total of 500 or more [37].

Stratified sampling was chosen as it reduces sampling error and ensures a greater level of representation when compared to simple random sampling [38]. It also ensures more precise estimates, provided that there is homogeneity within strata and heterogeneity between strata [38]. A questionnaire will be administered and biological samples collected (two micro-containers of blood for dried blood spot (DBS), plasma specimens and self-collected vulvo-vaginal swab samples (VVSS) to test for HIV infection, HIV incidence, STIs as well as pregnancy respectively).

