### Sampling strategy

A stratified cluster-based sampling design has been adopted, specifically:
The four districts will be considered as the primary strata.In order to reach 18,500 AGYW in each survey, a total of 1050 SALs will be selected and distributed between KZN and GP, proportional to the targeted sample size in each province (i.e. 10,500 AGYW in GP and 8000 in KZN), resulting in 450 SALs for KZN and 600 for Gauteng. A total of 300 SALs will be selected from eThekwini and 150 from uMgungundlovu; 300 from the City of Johannesburg and 300 from Ekurhuleni, this is proportional to the population size of the districts. uMgungundlovu is less than one third the size of eThekwini, however to ensure that estimates are reported with a higher level of precision for uMgungundlovu SALs were allocated in the ratio of 2:1 between uMgungunglovu and eThekwini.To achieve a minimum of 18 AGYW per SAL, taking into account that approximately 1 in 2 households have an eligible individual, and a non-response rate of 20%, 55 households will be randomly chosen within each SAL in order to attain a household-representative sample of AGYW [43].All eligible AGYW in the household will be approached for inclusion in the study.

The SAL sampling frame has been triangulated using 2011 census data [39], the 2007 Community survey data [38] and aerial imaging to determine the number of households and population estimate at the SAL level. The SAL sampling frame will be checked across these three data sources and estimates calculated according to province and district boundaries, whilst the population will be further classified according to race, gender and age. To adjust for unequal probability of selected SALs, non-response and to facilitate the interpretation of results at the provincial level, sampling weights will be used in all analyses. From a total of 19,366 SALs across the study area, approximately 1050 SALs will be selected to reach the targeted sample size. The sample size is based on the required number of AGYW (i.e 18,500) and working upwards to determine how many households need to be approached to realise this sample size. If one in two households have an AGYW [39], to obtain 18,500 we would need to approach 37,000 households (assuming they all agree to participate). However, we anticipate that 20% of households will not agree to participate and about 12.5% are unoccupied or invalid (so anticipate approaching 55,000 households).

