### Statistical considerations and sample size calculation

The sample size of 8000 per survey in the two KZN districts will have 80% power to detect a reduction of 40% in the HIV incidence rate at the 5% significance level given a false recent rate (FRR) of 0.01%, HIV prevalence of 25%, and an initial HIV incidence rate of 4 per 100 person years (py) [33]. A sample size of 10,500 per survey in the two GP districts will have 80% power to detect a 40% reduction in HIV incidence given a FRR of 0.01%, HIV prevalence of 25% and baseline incidence of 3/100py amongst AGYW aged between 12 and 24 years [8].

The aforementioned sample size calculations are based on detecting change in incidence and not the precision of individual estimates. However, the sample size of 8000 in KZN is adequate to estimate an HIV incidence rate of 4% with a coefficient of variation of 12%, corresponding to a confidence interval of (3.1–4.9%). The sample size in Gauteng of 10,500 will allow us to estimate the HIV incidence rate of 3% with a coefficient of variation of 12% and confidence interval of (2.28–3.72).

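### The power and precision figures name no design effect for a clustered, weighted survey, and at an assumed recency window of about 130 days they leave almost no room for one

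*Protocol article*

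**What the plan says.** In the protocol article, Statistical considerations and sample size calculation, the KZN claim is "The sample size of 8000 per survey in the two KZN districts will have 80% power to detect a reduction of 40" per cent. The test level is 5%, with no word on whether it is one- or two-sided, and the remaining KZN inputs are listed as "given a false recent rate (FRR) of 0.01%, HIV prevalence of 25%, and an initial HIV incidence rate of 4 per 100 person years". For Gauteng the claim is "A sample size of 10,500 per survey in the two GP districts will have 80% power to detect a 40% reduction in HIV incidence". Its inputs are the same false recent rate (FRR) and prevalence as in KZN, with baseline incidence set at 3 instead of 4. The section adds a CV of 12% for each province, with intervals of 3.1–4.9% (KZN) and 2.28–3.72% (Gauteng).

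Study design says that participants are "selected using a stratified cluster-based sampling approach, with districts representing strata", with the SAL as primary sampling unit. Sampling strategy fixes 450 SALs in KZN and 600 in Gauteng. Households per SAL are set "To achieve a minimum of 18 AGYW per SAL", and "All eligible AGYW in the household will be approached for inclusion in the study". Weights are to be applied in every analysis.

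The only inflation described is from 18,500 women to 55,000 households. It covers one eligible woman per two households, 20% refusal and 12.5% unoccupied or invalid dwellings. Study design's remark on sampling error is that stratification lowers it. No design effect or intracluster correlation (ICC) appears anywhere.

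**The concern.** Clustering within SALs, several women from one household and unequal weights all normally raise the variance above that of a simple random sample of the same size. A calculation that omits this promises more power and narrower intervals than the survey can deliver.

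The article makes the primary analysis a judgement on whether a 40% reduction was realised. If true power is below 80%, failure to show a reduction becomes more likely even when the target was met, and readers who trust the printed figure would misread such a result. This goes beyond detail that an article may leave to a fuller document: the figures and their inputs are printed, and so is the design they should reflect.

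**Working it through.** **Inputs from the article.** N = 8000 (KZN) and 10,500 (Gauteng) per survey; incidence I = 0.04 and 0.03 per year, falling by 40% to 0.024 and 0.018; prevalence p = 0.25; FRR = 0.0001; alpha 5%.

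**Assumed, because not stated.** MDRI 130 days (0.356 years); FRR cut-off T = 2 years; two-sided test; MDRI relative error 0 or 5%. The stated power also needs two equal surveys. The article describes one, which is a separate matter, so two surveys are granted here.

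**Formulas.**
- Recent fraction of the sample: R = I·(MDRI − FRR·T)·(1 − p) + FRR·p, and q = R/p.
- Relative variance: RV = DEFF·{1/[N·p·(1−p)] + q(1−q)/[N·p·(q−FRR)²]} + (MDRI error)².
- Power = Φ[(I1 − I2)/SE − 1.96], SE² = I1²·RV1 + I2²·RV2, without MDRI error.

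**Reproducing the plan at DEFF 1.**
- KZN baseline: R = 0.0107 (about 86 recent infections), q = 0.0428, RV = 0.000667 + 0.011238 = 0.011905, so CV = 10.9%. Adding 0.05² gives RV = 0.014405 and CV = 12.0%.
- KZN after a 40% fall: about 51 recent infections, RV = 0.019761.
- KZN power: SE = √(0.04²·0.011905 + 0.024²·0.019761) = 0.00552; 0.016/0.00552 = 2.90; Φ(2.90 − 1.96) = 82.7%.
- Gauteng: RV = 0.012061 and 0.020058, SE = 0.00417, power 82.1%; CV 11.0%, or 12.1% with 5% MDRI error.
- Intervals with 5% MDRI error: 3.06–4.94% and 2.29–3.71%, against the stated 3.1–4.9% and 2.28–3.72%.

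**Room left for a design effect.** Two-sided 80% power needs a ratio of 1.96 + 0.84 = 2.80. The largest tolerable DEFF is (2.90/2.80)² ≈ 1.07 in KZN and about 1.06 in Gauteng.

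**Weighting alone.** The Kish factor is n·Σ(N_d²/n_d)/(ΣN_d)², with the SAL counts as n_d and the Table 1 female populations aged 10–24 as N_d (a proxy for ages 12–24).
- KZN: 450·(500,214²/300 + 153,722²/150)/653,936² = 1.043.
- Gauteng: 600·(584,104²/300 + 395,866²/300)/979,970² = 1.037.

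**Effect of a larger DEFF (MDRI 130 days, two-sided).** Power is without MDRI error; CV and interval include 5%.

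| DEFF | Power KZN / Gauteng | CV KZN / Gauteng | Interval KZN | Interval Gauteng |
|---|---|---|---|---|
| 1.0 | 82.7% / 82.1% | 12.0% / 12.1% | 3.06–4.94% | 2.29–3.71% |
| 1.1 | 79.0% / 78.4% | 12.5% / 12.6% | 3.02–4.98% | 2.26–3.74% |
| 1.2 | 75.4% / 74.8% | 13.0% / 13.0% | 2.98–5.02% | 2.23–3.77% |
| 1.5 | 65.8% / 65.2% | 14.3% / 14.4% | 2.88–5.12% | 2.16–3.84% |

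Cluster size is 8000/450 = 17.8 or 10,500/600 = 17.5. By DEFF = 1 + (m − 1)·ICC, a DEFF of 1.2 corresponds to an ICC of about 0.012 and 1.5 to about 0.030.

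**Sensitivity to the missing inputs (KZN, no MDRI error).** The DEFF compatible with two-sided 80% power is 0.99 at 120 days, 1.07 at 130, 1.24 at 150 and 1.64 at 200. One-sided, it is 1.36 at 130 days and 1.57 at 150.

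**The household step.** 18,500 × 2 = 37,000, and 37,000/(0.80 × 0.875) = 52,857, close to the stated 55,000. A design effect would have to sit inside the 18,500, and nothing in the article says that it does.

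**The case against.** A reader might infer that the figures can be reproduced only with DEFF 1, and that the survey therefore certainly lacks its stated power and CV. The documents do not support that. Other combinations fit too: one-sided at 150 days with DEFF 1.5 gives 81.5% power in KZN and, without MDRI error, a CV of 12.45%. Without MDRI error at 130 days, the CV at DEFF 1 is 10.9%, so a stated 12% would itself allow a DEFF of about 1.21. For the same reason, inflating the whole 12% by √1.5 to 14.7% is too harsh, because any MDRI error inside it does not grow with clustering.

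The outcome is also rare. With about 1.1% of KZN participants classed as recent, ICC = k²R/(1 − R), where k is the between-SAL coefficient of variation of the true recent-infection proportion. DEFF 1.2 from clustering alone needs k of about 1.05, and DEFF 1.5 needs 1.66. With k = 0.5 and the weighting factor, DEFF is about 1.09 and KZN power 79.3%; with k = 0.75, 1.15 and 77.2%. A loss of only a few points is therefore plausible.

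These arguments stand, and they limit the size of the claim. They do not show that clustering was allowed for. Nor is a variance formula being requested: the article already names the SAL as primary sampling unit and commits to weights.

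**Conclusion.** The point holds in conditional form. The article prints power, CV and intervals for a clustered, weighted survey without a design effect among the inputs. At an assumed MDRI of about 130 days and a two-sided test, DEFF 1 reproduces the figures closely. The margin above 80% is then a DEFF of about 1.07, of which district weighting takes about 1.04 before any SAL or household clustering.

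Under those assumptions, power would be about 75% at DEFF 1.2 and 65–66% at DEFF 1.5. These are scenarios, since the article gives no ICC, MDRI, MDRI error or sidedness. What is established is that a reader cannot tell whether clustering was allowed for, and that the simplest reading of the stated inputs is that it was not.

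**What to change.** In the sample size section, state the MDRI, its relative error, whether the 5% is one- or two-sided, and the design effect used. The design effect could come from the earlier incidence survey in uMgungundlovu, noting that it covers only one of the four districts, or be shown as a range such as 1.1–1.5. Then restate power, CV and expected interval for KZN and Gauteng on that basis. If a design effect is already inside the 8000 and 10,500, one sentence giving its value, together with the MDRI, settles the matter.

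The cost is text and a recalculation. Unless one was already included, the stated figures become somewhat less favourable. No added enrolment is needed.

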## Background

Adolescent girls and young women (AGYW) in sub-Saharan Africa remain the sub-population most susceptible to HIV infection [1]. In 2017, approximately 65% of all new HIV infections occurred in sub-Saharan Africa [2], with AGYW accounting for 74% of these infections, with more than 1000 HIV acquisitions amongst adolescents occurring daily [2, 3]. South Africa (SA) currently has the largest HIV epidemic in the world, with an estimated 7,520,000 people living with HIV (PLHIV) in 2018 [4]. A National surveillance study in 2017 estimated that 20.0% (95% CI 18.7–21.4) of South Africans fifteen years and older, were living with HIV [5] . In 2017, the prevalence amongst males was lower compared to females (4.7% versus 5.8% among those aged 15–19 years, and 4.8% versus 15.6% among those aged 20–24 years). The highest HIV-incidence (1.5%) is amongst South African females aged 15–24 years compared to 0.5% amongst young men their own age, translating into over 66,000 new infections amongst AGYW in South Africa (SA) in 2017 [5].

Several factors contribute to the observed increased rates of HIV acquisition amongst AGYW. Young women are biologically more susceptible to acquiring HIV than men. The risk of HIV transmission during unprotected vaginal intercourse is greater for women than men; and the risk for AGYW is further heightened because their vaginal tracts are immature and tissue tears occur more easily from sexual activity [6]. Furthermore, a study concluded that women with genital inflammation had an almost three-fold higher risk of HIV acquisition [7]. The risk of acquiring HIV also increases in the presence of sexually transmitted infections (STIs), with the majority of STIs occurring in young people under 25 years of age [8–10]. The estimated prevalence of STIs in South Africa among female clinic or community populations aged 15 to 24 years old was 20.6% for chlamydia, 8.9% for gonorrhoea, 20.0% for trichomoniasis, 53.7% for HSV-2, and 52.4% for bacterial vaginosis [11].

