### Study aim

The aim of this study is to determine the impact of the DREAMS initiative on HIV incidence amongst a household-based representative sample of AGYW (12–24 years) in four of the five districts in KwaZulu-Natal (KZN) and Gauteng (GP), South Africa. An HIV incidence baseline will be estimated primarily using incidence findings from existing studies. HIV incidence in the South African National HIV Prevalence, Incidence, Behaviour and Communication Survey Study (SABSSM) used a similar incidence bio-marker-based methodology to one adopted for this study. The HIV incidence findings for AGYW 15–24 years at the national level was 2.54% (95% CI 2.04–3.04) in 2012. An earlier longitudinal study on HIV uninfected 14–30 year old women, undertaken between March 2004 and May 2007, revealed that HIV incidence in young girls below the age of 18 years was 4.7 [95% Confidence interval (CI) 1.5–10.9) compared to 6.9 (95% CI 4.8–9.6)/100 women years (wy) in those aged 18 - 30 [32]. The HIV Incidence Provincial Surveillance System (HIPSS) situated in uMgungundlovu, KZN, included two cross-sectional surveys between June 2014 and June 2015 and between July 2015 and July 2016. The HIPSS study population was drawn from uMgungundlovu, the same area for this study. The HIPSS incidence in adolescent girls 15–19 years was 4.63% (95%CI, 3.29–6.52) and 4.00% (95% CI, 2.74–5.85) for women 20–24 years old in the 2014 survey [33].

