## Methods/design

### Study setting

The four study districts (City of Johannesburg, Ekurhuleni, uMgungundlovu and eThekwini) consist of an estimated 12,073,421 individuals. uMkhanyakude, the fifth DREAMS district, is not part of this evaluation.

The province of KZN remains the worst affected by HIV with an overall prevalence of 15% amongst 15 to 49 year old inhabitants in 2015 [34]. The two districts of interest within KZN, uMgungundlovu (20% HIV prevalence in 2016) and eThekwini (16.8% HIV prevalence in 2016) are among those with the highest HIV prevalence in South Africa [34]. eThekwini contains the third-largest city in the country (Durban), which is the busiest port on the African continent and the main economic hub within the province of KZN [35]. About 68% of eThekwini is considered rural and 32% urban.

uMgungundlovu is the second largest district in KZN after eThekwini and is located in central KZN. uMgungundlovu includes traditional settlements or farmlands, informal, rural and urban settlements. Its local municipalities are largely rural, while the Msunduzi Municipality is highly industrialized. The largest city within the uMgungundlovu district is Pietermaritzburg, which is also the capital of KZN.

The Gauteng province (GP), whilst geographically the smallest, is the most populous province in South Africa. GP has the fifth highest provincial HIV prevalence in the country with a prevalence of 11.1% in 2016 [34]. The HIV prevalence in the two study districts, City of Johannesburg and Ekurhuleni is 11.1 and 14.3% respectively [8]. These districts are densely populated. Whilst highly urbanised with a diverse economy, large urban townships including Katlehong and Tokoza which form part of the Ekurhuleni district. The HIV prevalence amongst AGYW in the City of Johannesburg and Ekurhuleni was estimated to be is 3% in 2012 [36].

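### Gauteng's 80% power rests on a 25% HIV prevalence that the protocol's own figures contradict and a 3/100py incidence that they do not support for ages 12–24

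*Protocol article*

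**What the plan says.** Under Statistical considerations and sample size calculation, the protocol states: "A sample size of 10,500 per survey in the two GP districts will have 80% power to detect a 40% reduction in HIV incidence". The inputs are a false recent rate of 0.01% and "HIV prevalence of 25% and baseline incidence of 3/100py amongst AGYW aged between 12 and 24 years", with a literature citation. The same section says that this sample will "estimate the HIV incidence rate of 3% with a coefficient of variation of 12% and confidence interval of (2.28–3.72").

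Other sections give different figures:

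- Study setting, on the same two districts: "The HIV prevalence amongst AGYW in the City of Johannesburg and Ekurhuleni was estimated to be is 3% in 2012".
- Background: national female prevalence in 2017 was 5.8% at ages 15–19 and 15.6% at 20–24.
- Study aim: "The HIV incidence findings for AGYW 15–24 years at the national level was 2.54% (95% CI 2.04–3.04) in 2012".
- Background, for 2017: "The highest HIV-incidence (1.5%) is amongst South African females aged 15–24 years".

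The text does not reconcile the planning inputs with these figures, and no other Gauteng-specific incidence appears.

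**The concern.** The 25% prevalence is about eight times the protocol's own figure for these districts and exceeds both national age-specific figures for young women. In Gauteng, only the antenatal prevalences in Table 1 (27.5% and 33.5%) are of that size. They describe pregnant clinic attenders, not a household sample that starts at age 12.

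The 3/100py is applied to ages 12–24, while the national incidences start at 15. Adding 12–14 year olds, in whom incidence should be lower, moves the expected rate down.

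The primary analysis asks whether a 40% reduction was achieved. Power for that question depends mainly on the number of recent infections found. If true baseline incidence is below the planned value, a non-significant Gauteng result could be read as programme failure when the comparison was simply too weak.

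**Working it through.** **Inputs from the protocol.** n = 10,500 per survey; 40% reduction; false recent rate (FRR) 0.01%; prevalence P = 25%; incidence I = 3/100py; 5% significance level (stated for KwaZulu-Natal, taken as two-sided here).

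**Assumptions not in the protocol.** Mean duration of recent infection (MDRI) 118–141 days; recency cut-off T = 2 years; two independent surveys; no design effect; no uncertainty in MDRI or FRR.

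**Formulas** (recency-assay estimator, delta-method variance).

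- Proportion of positives classed as recent: R = I(1−P)(MDRI − FRR·T)/P + FRR
- CV² = (1/(nP)) · [1/(1−P) + R(1−R)/(R−FRR)²]
- Power = Φ(0.4·I/SE − 1.96), where SE² = (I·CV₁)² + (0.6·I·CV₂)²

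**Step 1: reproduce the stated figure, MDRI 130 days.**

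- MDRI − FRR·T = 130/365.25 − 0.0002 = 0.3557 years.
- Before: R = 0.03 × 0.75 × 0.3557/0.25 + 0.0001 = 0.0321, or 10,500 × 0.25 × 0.0321 ≈ 84 recent infections; CV₁ = 0.110.
- After (1.8/100py): R = 0.0193, about 51 recent infections; CV₂ = 0.142.
- SE = √[(0.03 × 0.110)² + (0.018 × 0.142)²] = 0.00417. Power = Φ(0.012/0.00417 − 1.96) = 0.82.

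Power is 0.78 at 118 days and 0.85 at 141 days, so 80% follows from the stated inputs with a window between 118 and 130 days. The CV is 10.5–11.5%, close to the stated 12%. A 12% CV at 3% gives 3 ± 1.96 × 0.36 = 2.29–3.71, or exactly 2.28–3.72 with a multiplier of 2.

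**Step 2: change prevalence only.** At 3% prevalence there are 10,500 × 0.97 = 10,185 susceptible women instead of 7,875. Recent infections rise from about 84 to 109, and power rises from 0.82 to 0.91 (MDRI 130).

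**Step 3: what prevalence and incidence do the protocol's figures imply?**

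- Prevalence: the mean of 5.8% and 15.6% is 10.7% at ages 15–24. With uniform ages and none infected at 12–14 it is 10.7 × 10/13 = 8.2%. With the district figure of 3%, a range of about 3–10% is reasonable.
- Incidence: with uniform ages and negligible incidence at 12–14, 2.54 × 10/13 = 1.95%. The confidence limits scale to 2.04 × 10/13 = 1.57 and 3.04 × 10/13 = 2.34.

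**Step 4: power with n = 10,500 per survey** (ranges over MDRI 118–141 days).

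| Baseline incidence | P = 25% | P = 10% | P = 3% | CV at P = 3–10% |
|---|---|---|---|---|
| 3.00% | 78–85% | 85–91% | 88–93% | 9.3–10.5% |
| 2.54% | 71–79% | 79–86% | 82–88% | 10.1–11.4% |
| 1.95% (2.54% diluted) | 60–68% | 68–76% | 71–79% | 11.5–13.0% |
| 1.50% | 49–56% | 57–64% | 60–68% | 13.1–14.8% |

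At 3% prevalence, 80% power is kept down to an incidence of about 2.0–2.4%, depending on the window.

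**The case against.** The best defence is that the power statement is conditional: it gives 80% for named inputs, and those inputs do produce it. That stands. There is no arithmetic error, and the interval agrees with its CV.

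Four further points limit the concern:

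- **Prevalence.** A reader might infer that a 25% prevalence inflates the stated power. It does the reverse: a high assumed prevalence is conservative for power. The contradiction in the text remains, but it does not by itself cost power.
- **The 2.54% figure.** A reader might infer that it refutes 3/100py. It does not: it is national, its interval reaches 3.04, and at 2.54% with 3–10% prevalence both the power and the 12% CV roughly survive. The difficulty comes only from the age range. The diluted interval of 1.57–2.34 excludes 3, but that rests on two age assumptions that the protocol does not make. The source cited for 3/100py cannot be checked from the protocol.
- **The 1.5% figure.** It is a 2017 national rate, from the period of the survey and after DREAMS was introduced in 2014, so it is a weak baseline. The fall from 2.54% to 1.5% is already 41%, about the effect sought. Diluting 1.5% as well would bring power to about one half, but that stacks an age assumption on a follow-up-period rate, and the documents do not support it as a planning value.
- **The interval.** It might be called too narrow. That is true only in relative terms: at 1.5% the absolute half-width is about 0.4 points, against 0.72 in the protocol.

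What remains is a contradicted prevalence, and an incidence without visible support for a sample that includes 12–14 year olds.

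**Conclusion.** The concern stands as one about inputs. The protocol's district and national figures contradict the 25% prevalence, and its 15–24 incidences do not support 3/100py at ages 12–24. The documents do not show that 80% power is wrong outright. At 3–10% prevalence, power is about 79–88% at 2.54%, 68–79% at 1.95%, and 57–68% at 1.5%, where the CV is 13–15%.

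The 1.95% assumes uniform ages and negligible incidence at 12–14. The power ranges also assume the two surveys implied by the sample-size wording, although the study design describes a single one. That discrepancy is a separate matter. The sample is clustered, so ignoring a design effect makes these figures optimistic. Nothing here was calculated for alternative inputs in KwaZulu-Natal, and no conclusion is drawn there.

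**What to change.** In the sample-size section, for Gauteng:

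1. Replace the 25% prevalence with values consistent with the Background and Study setting sections, about 3–10%.
2. Use, and justify, a baseline incidence that applies to ages 12–24 in these districts.
3. Replace the single 80% power and 12% CV claims with a short table of power and relative precision over about 1.5–3/100py.
4. State the recency window used.

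The cost is a recalculation and a paragraph of text. No added enrolment is needed, though the stated power may become less favourable.
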